## Abstract

**Background:**

Pancreatic ductal adenocarcinoma (PDA) is one of the most aggressive malignancies with marked resistance to chemo- and radiotherapy. PDA-cancer stem cells (CSCs) are not targeted by current therapies and may be a reason for poor prognosis. Studies indicate that diets rich in cabbage, broccoli, and cauliflower offer cancer preventative and therapeutic benefits. Recent experimental studies have confirmed these findings and demonstrated that isothiocyanate, sulforaphane, and the polyphenol, quercetin, effectively reduced tumor growth and enhanced the sensitivity of the cancer cells to current chemotherapeutics. The aim of the present study is to test the feasibility of a randomized controlled trial on the application of freeze-dried broccoli sprouts in patients with advanced PDA.

**Methods and study design:**

The study is designed as a prospective randomized, double-blinded pilot trial with a treatment and a placebo-controlled arm in a single center setting. A total number of forty patients (18 years or older) in two parallel groups with advanced, surgically non-resectable PDA under palliative chemotherapy are planned for recruitment. Patients in the treatment group will receive fifteen capsules of the study substance per day (90 mg of active sulforaphane) during the chemotherapy treatment course. Patients in the placebo group will receive the same capsule size and portion distribution with inactive substances (mainly methylcellulose). The follow-up duration is one year. Feasibility of the study substance, adverse effects, and patient compliance, as well as levels of serum tumor markers (CEA, CA 19-9), quality of life, and patient overall survival rates will be assessed at defined points of time.

**Discussion:**

The POUDER trial is expected to transfer promising experimental and epidemiological data into a clinical pilot study to assess the effectiveness of broccoli sprout extracts in the treatment of advanced PDA. The study objectives will provide data on the clinical feasibility and acceptability of a supportive treatment option accompanying palliative chemotherapy. Based on these results, future clinical studies to create further evidence in this field are possible.

**Trial registration:**

The POUDER trial has been registered at ClinicalTrials.gov with an ID NCT01879878 and WHO with an ID U1111-1144-2013 on June 13^th^ 2013.

## Background

Pancreatic ductal adenocarcinoma (PDA) is the fourth most common cause of cancer-related deaths worldwide. It is one of the most aggressive and lethal malignancies, with a 5-year survival rate of 6% in Europe and the United States, and a median survival time of 4 to 6 months [1-3]. With an incidence proportionally correlated to age [1], the numbers of estimated new cases and PDA-related deaths for 2013 in the United States alone are 45,220 and 38,460, respectively [4]. Despite standardization and advances in surgical and systemic treatment options, curative surgical intervention is possible in only 20% of the patients [5], due to the cancer’s initial asymptomatic course. Most patients present with an advanced stage of disease and can therefore only be treated in a palliative intention, which explains the nearly similar rates of incidence and mortality [1,6]. PDA-specific molecular aberrations, intense desmoplastic stroma reaction, and hypoxia are some of the factors that presumably cause the poor outcome [7].

Recent research data strongly suggest that cancer is a stem cell disease [8,9]. The small subpopulation of cancer stem cells (CSCs) within the tumor mass is thought to survive during conventional cytotoxic therapy due to its defense and survival mechanisms [10]. CSCs are believed to be capable of self-renewal and differentiation, thereby generating a heterogeneous cell population of the original tumor [8,11,12]. In addition, it has been proposed that CSCs mediate uncontrollable growth, therapy resistance, cell invasion, and metastasis [13]. Markers for CSCs have been identified in various tumor entities, including PDA, and selected marker-positive cell fractions are able to reconstitute the original tumor in immunodeficient mice [14].

In a review published in 2007, the American Institute for Cancer Research (AICR) drew attention to the benefits of increased cabbage consumption in PDA patients [15]. These results were not restricted to the pancreas, as two recent epidemiological, prospective nutrient studies demonstrated significant inhibition of metastases seeding in patients with prostate cancer [16,17]. Kirsh, *et al*. observed the significantly decreased risk of extra-prostatic manifestation of prostate cancer (stage III or IV tumors) correlated with an increase in the consumption of cruciferous vegetables, in particular broccoli which is rich in sulforaphane and quercetin (*P* = 0,02) [16]. The benefits inferred by sulforaphane, which is derived from mustard oil, and its inactive glycoside precursor, glucoraphanin (present in high concentrations in broccoli and its sprouts), have been thoroughly investigated [18,19]. Sulforaphane is believed to target CSCs through the downregulation of NF-κB [18]. This observation was first discovered in PDA and has also been confirmed for breast and prostate cancer [20,21]. Consequently, these substances may serve as an alternative treatment option for PDA; by exhausting pancreatic CSCs, the tumor sensitivity to chemotherapeutics, such as sorafenib, gemcitabine, cisplatin, doxorubicin, and 5-fluorouracil, may be significantly improved [20,22,23].

### Trial rationale

Epidemiological and animal studies in various cancer entities [15-17,20,24-29] clearly demonstrate that broccoli sprouts, rich in sulforaphane, have a tumor-suppressive potential [18]. However, to date there has been no routine clinical application of broccoli sprouts or their isolated phytochemical substances. The aim of this pilot study is to evaluate, for the first time, the feasibility and clinical impact of a daily application of encapsulated, freeze-dried broccoli sprouts in PDA patients in a palliative setting as a chemotherapy-supporting agent. The results of the study could consequently serve as the rationale for the design of further clinical trials.

## Methods/Design

The ethics committee of the University of Heidelberg has approved the POUDER trial as a monocentric, prospective, randomized, placebo-controlled clinical pilot study with two parallel groups (placebo versus verum) and provided the trial ethical approval (reference S-347/2009). Forty eligible patients receiving palliative chemotherapy, who meet the inclusion criteria (Table 1), with advanced, non-resectable PDA treated at the European Pancreas Center in Heidelberg, will be enrolled after signing informed consent. Approximately 15 to 20 PDA patients who meet the study inclusion criteria are treated in the outpatient department of the European Pancreas Center per month. Therefore, a short recruitment period of 3 to 4 months is expected. Exclusion criteria are a known intolerance to broccoli or its ingredients, impaired mental status, language problems, or a refusal of participation. Due to the nutrition supplemental character of the trial, sufficient oral intake is a prerequisite for inclusion in the study that is, the patients should not have symptoms or signs of indigestion or problems with the passage of food (nausea, vomitus, presence of nasogastric tube) (Table 1).

**Table 1 T1:** Trial inclusion and exclusion criteria

**Inclusion criteria**	**Exclusion criteria**
Patients ≥18 years	Intolerance to broccoli or its ingredients
Advanced, surgically non-treatable PDA^a^	Impaired mental status or language problems/barriers
Written informed consent	
Intact gastric emptying	
Palliative chemotherapy	

^a^Patients who receive surgical exploration, intraoperative biopsy, and/or palliative bypass interventions (bileodigestive anastomosis and/or gastroenterostomy because of preoperative cholestasis or impaired gastric emptying due to a tumor-mass effect) will be included in this trial. PDA, pancreatic ductal adenocarcinoma.

### Trial objectives

The objective of this pilot trial is to evaluate the feasibility of nutritional supplements rich in sulforaphane and quercetin, administered via encapsulated, freeze-dried broccoli sprouts, in patients with advanced pancreatic cancer undergoing treatment with palliative chemotherapy. In this context, given that patients are supposed to take 15 capsules per day, the principal objective of this trial is to test if the daily intake is possible. In order to achieve the effective sulforaphane dose as extrapolated from our previous animal experiments, the capsules should be taken all 15 at once, however with an acceptable pause of few minutes in between.

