### Randomization and blinding

A 1:1 randomization will be performed and patients will be assigned with a randomization number. In case there are dropouts, these patients will be replaced and the new patients will be assigned in an identical manner. If a patient drops out of the study at month 6 due to his/her own decision, the patient data will be removed from the trial completely, including any data generated prior to the withdrawal. If a patient passes away during the first 6 months, the data will be used. If the urine probes reveal that a patient from the broccoli sprouts group did not consume the broccoli sprouts daily or if a patient from the placebo group had a high dietary intake of isothiocyanates, the data from these patients will not be used, but the patient will be replaced by a new patient, even if a patient drops out between months 9 to 12. This case will extend the duration of the study. Randomly generated numbers will be allocated to the two groups in balanced permuted blocks using a number generator (validated software, SAS). In order to avoid any possibility of predicting the group allocation, the length of the blocks will be fixed in a separate document and this information will be withheld from the study site. A data sheet that links the group allocation with the randomized number of the patient will be sealed in pre-produced, non transparent envelopes labeled with the arbitrary patient numbers and these envelopes will be used in consecutive order. In order to be able to perform a retrospective control of the compliance to randomization, basic patient data, including the day on which the patient’s number was assigned, will be noted on the data sheet. After completing the trial, all unopened envelopes will be delivered to the data management center for comparison to the allocated, randomized patient numbers and examination and evaluation of the thoroughness of the trial.

The investigators, patients, and assessors of the POUDER trial will be blind to the patients’ study treatment courses. The principal investigator (PI) will be provided with a set of sealed envelopes containing information on patients’ trial drugs, one for each patient number. These envelopes are to be opened only under imperative circumstances (medical indication to know the substance in use by the subject).

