### Data management and statistical analysis

The trial investigator or a designated representative (sub-investigator) will document all data acquired during the trial in a case report form (CRF) on the day of the routine visit. All missing or inconsistent data will be reported and inferred. Upon completion, all CRFs must be officially reviewed and signed by either the investigator named in the trial protocol or by a designated sub-investigator. In order to assure the highest data quality and accurate transfer from the CRF to the database, a double data-entry method will be performed. After completing the trial, the PI will retain the original CRFs.

Totality, validity, and plausibility of the data will be examined by validating programs that will generate queries that must be clarified by the investigator. All findings, both clinical and overall survival, imaging of disease stages, quality of life, and biochemical analyses will be noted in the subject’s CRF.

As this is a pilot study, no sample size calculation was performed. A sample size of 20 patients per study group has been deemed sufficient for the study objectives. The sample size of 20 patients per group is speculative at this time and it is based on comparable patient numbers used in similar ongoing and recently completed patient studies with broccoli sprout extracts. For example, the Pittsburgh pilot study evaluating sulforaphane in atypical nevi-precursor lesions enrolled 18 patients (http://clinicaltrials.gov/ct2/show/NCT01568996?term=NCT01568996&rank=1) and another study performed at OHSU Knight Cancer Institute for examination of sulforaphane in treating patients with recurrent prostate cancer (http://clinicaltrials.gov/ct2/show/record/NCT01228084?term=sulforaphane&rank=1) enrolled 20 patients.

Depending on data characteristics, descriptive statistics of the monitored parameters will be presented as mean values and SD or median values and IQR. Descriptive *P*-values of the *t*-test or the Mann-Whitney *U*-test comparing the treatment groups will be given, together with the corresponding 95% CI. Categorical parameters will be presented as relative and absolute frequencies, and comparisons will be performed using the Fisher exact test.

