From the available studies, it can be noted that there is a positive correlation between the consumption of broccoli and an increased efficacy of chemotherapy [27,40]. However, to date this is not based on high-level evidence trials. The POUDER trial will not interfere with any palliative chemotherapy or targeted therapy as these substances typically do not require any food restrictions. Consequently, patients who participate in PDA trials can simultaneously participate in a broccoli nutritional study. However, compounding effects of the intake of broccoli sprouts might have an influence on the results of any parallel trial due to the potential benefit of their application. The present trial has to be regarded as a test of feasibility. Participation in other treatment schemes - regardless of whether or not standard or study substances are applied - was not defined as a contraindication for inclusion. As patients suffering from tumor diseases are often encouraged to make healthy changes in their lifestyle, other phytotherapies may be expected. Yet, the effects of the chosen high dosage of the broccoli sprout extract will probably overpower the effects of any other nutritional substance.

A possible side effect of high broccoli sprout intake may be meteorism, which is a common phenomenon associated with cabbage consumption. Other effects include the prominence of the rotten-egg odor. During the metabolic breakdown of cabbage in the digestive tract, sulfur in the glucosinolates [41] is converted into the rotten-egg chemical, hydrogen sulfide, by gut bacteria. These potential side effects may be uncomfortable, but are considered to be insignificant in the overall context of a promising therapy for an advanced tumor disease.

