With regard to sulforaphane, its modus operandi is believed to be as an indirect antioxidant that helps to protect healthy cells from oxidative damage and reduce the short- and long-term harmful effects of cancer treatment [42]. However, concern has been raised that antioxidant supplements may also protect tumor cells during chemotherapy, thereby compromising treatment efficacy [42,43]. This has resulted in controversy over the guidelines for the use of vitamin supplements during cancer treatment. This issue was examined in an experimental human PDA xenograft model in mice. In this setup, sulforaphane did not protect tumor cells; instead, it increased the effect of gemcitabine, cisplatin, doxorubicin, 5-fluorouracil, sorafenib, and TRAIL [20,22,23,27].

In closing, the POUDER trial is the first clinical pilot trial to test the feasibility of an intake of freeze-dried broccoli sprouts as an additive of palliative chemotherapy in surgically non-resectable, advanced pancreatic cancer. Depending on the results of this pilot trial, a hypothesis for a confirmatory trial in the field will be generated and a consecutive RCT is planned.

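### The principal objective, whether 15 capsules a day can be taken, has no stated criterion; the written analysis does not address it, and the removal rules delete the patients who fail it

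*Protocol article*

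**What the plan says.** Under Trial objectives, the article states that "the principal objective of this trial is to test if the daily intake is possible", given 15 capsules per day. The Discussion adds that "The present trial has to be regarded as a test of feasibility". Under Outcome measures, intake is recorded in a patient diary (regularity and amount), and urinary isothiocyanates monitor compliance. Under Trial interventions, both arms take 15 capsules of identical size.

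Under Data management and statistical analysis, the rule for a categorical outcome reads "Categorical parameters will be presented as relative and absolute frequencies, and comparisons will be performed using the Fisher exact test". Continuous outcomes get means or medians with descriptive between-group P-values and 95% CIs. Median survival and one-year survival get 95% CIs.

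On size, the same section says "As this is a pilot study, no sample size calculation was performed", then "A sample size of 20 patients per study group has been deemed sufficient for the study objectives", and then "The sample size of 20 patients per group is speculative at this time". The support offered is the enrolment of other broccoli sprout studies, with 18 and 20 patients given as examples.

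Under Randomization and blinding, dropouts are replaced. A patient who leaves at month 6 by own decision has all data removed. A verum patient whose urine shows that the sprouts were not taken daily is not used and is replaced. Data from patients who die in the first 6 months are kept.

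**The concern.** The question named as principal is whether patients can manage the daily intake. The article does not say how much intake makes one patient a success, or what proportion of successes would count as feasible. The analysis it does write compares the arms, which is a different question. The data rules then remove patients who did not manage the intake or who chose to stop.

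The risk is a feasibility conclusion shaped by choices made after the intake data are known: the definition of success, the threshold and the denominator. A percentage from about 20 patients, shown without an interval, would also look more certain than it is.

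**Working it through.** **Inputs.** From the article: 20 patients per group (2 × 20 = 40, which agrees with the stated total), 1:1 allocation, 15 capsules daily in both arms, and the removal rules above. The stated 20 cannot be reproduced, because no rate, threshold, error level or power is given. All true rates, pass marks and floors below are therefore assumptions.

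**Step 1. Does the Fisher test address the objective?** Its null hypothesis is that the success probability is the same in both arms. Suppose 8/20 succeed in each arm, or 18/20 in each arm. Both tables give P = 1, although intake is 40% in one case and 90% in the other. The test cannot separate a regimen that most patients fail from one that most manage.

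**Step 2. How precise is a proportion from 20 patients?** Exact (Clopper-Pearson) 95% limits for x of n are the 2.5% quantile of Beta(x, n − x + 1) and the 97.5% quantile of Beta(x + 1, n − x).

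| Successes of 20 | Observed | Exact 95% CI |
|---|---|---|
| 14 | 70% | 45.7% to 88.1% |
| 15 | 75% | 50.9% to 91.3% |
| 16 | 80% | 56.3% to 94.3% |
| 17 | 85% | 62.1% to 96.8% |
| 18 | 90% | 68.3% to 98.8% |
| 19 | 95% | 75.1% to 99.9% |

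The fewest successes that put the lower limit above 50%, 60% or 70% are therefore 15, 17 or 19.

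**Step 3. How likely are those counts?** With X ~ Binomial(20, p) and an assumed p = 0.80:
- P(X ≥ 15) = 0.804
- P(X ≥ 17) = 0.411
- P(X ≥ 19) = 0.069

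If p = 0.90, P(X ≥ 19) = 0.392.

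**Step 4. What does a threshold chosen later do?** Take an assumed p = 0.70 and judge only the observed percentage. The chance of reaching 50%, 60%, 70%, 80% or 90% (10, 12, 14, 16 or 18 of 20) is 0.983, 0.887, 0.608, 0.238 or 0.035. The conclusion depends heavily on which mark is used.

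**Step 5. What do the removal rules do?** Suppose 5 verum patients are removed as non-takers and replaced, and the 20 retained patients all succeed. Among retained patients the rate is 20/20 = 100% (exact lower limit 83.2%). Among all randomized to verum it is 20/25 = 80% (exact 95% CI 59.3% to 93.2%). The 5 are hypothetical, but the direction is not: removing failures can only raise the rate.

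**The case against.** The strongest reply is that this is a descriptive pilot reported in a condensed article. Pilots need no hypothesis test, the word test sits beside evaluate in the same section, and a responder definition may be in the full protocol or SAP, neither of which is shown. The article also calls its sample size speculative, so it claims no statistical basis for it.

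Much of this stands. A reader might infer that a formal test against a null rate is required. It is not: an estimate with an interval, read against a pre-set criterion, is enough. A reader might infer that the plan gives no interval for any single-group proportion. It does so for one-year survival, but not for intake. A reader might infer that a go/no-go decision on the next trial hangs on the intake rate. The Discussion says only that the results will shape a confirmatory hypothesis and that a further randomized trial is intended, and Outcome measures links hypothesis generation to differences between the arms. No decision rule on intake is stated.

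The figures also depend on choices. The working uses verum only and a two-sided 95% bound. With a one-sided 5% level, a 70% floor needs 18/20 and is passed with probability 0.677 at a true rate of 90%, against 0.392 for 19/20. Pooling all 40 patients as a measure of capsule burden, at one-sided 5%, gives power 0.839 for 60% against 80% and 0.900 for 70% against 90%.

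What does not fall away is the mismatch within the text shown. The article sets out its principal objective, analysis, size rationale and data-removal rules. As written, the analysis does not address the objective, and the removal rules delete failures on it.

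**Conclusion.** The point holds in this form: no criterion is stated for the principal objective, the written categorical analysis does not answer it, no interval is written for an intake proportion, and the removal rules push any rate among retained patients towards 100%. The sufficiency of 20 per group is asserted without anything to check it against.

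It would go too far to conclude that 20 per group is inadequate. At an assumed true rate of 80% and a two-sided 95% bound, 20 verum patients give an 80% chance of clearing a 50% floor, 41% for 60% and 7% for 70%. Whether that is enough depends on a floor that only the sponsor can set. An unseen full protocol or SAP could supply a criterion, but the removal rules in the article would still need to be reconciled with it.

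**What to change.** Before any intake data are reviewed, even pooled and blinded, fix the following. Waiting until unblinding is too late, because pooled diary intake is visible while the trial is blinded.

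1. **Patient-level success:** a sponsor-set minimum share of scheduled capsules taken by diary, while the patient is alive and scheduled to take them. Urinary isothiocyanates serve as a supporting check.
2. **Denominator:** all patients randomized to verum, including those later replaced. Non-takers and voluntary withdrawals count as failures. The data-removal rules under Randomization and blinding must be amended so that these patients stay in this analysis.
3. **Reporting:** the proportion with its exact 95% CI. Feasibility is claimed only if the lower limit exceeds a sponsor-set floor. The both-arm capsule-burden rate is a secondary summary, and the Fisher test is descriptive.
4. **Sample size text:** replace the sufficiency claim with what 20 verum patients deliver: an exact 95% CI of about 56% to 94% at 16/20, and at least 15, 17 or 19 successes for a lower limit above 50%, 60% or 70%, with chances of 80%, 41% or 7% at an assumed true rate of 80%. If replacements take the number randomized to verum above 20, recompute the counts for the actual number.

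No particular floor is prescribed. The cost is wording and one exact interval on data already collected, with no extra patients or procedures. The downsides are that the sponsor commits to a floor in advance and that the stated sufficiency looks less favourable.
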